### 2.5. Observational Parameters and Clinical and Laboratory Assessments

Participants in the clinical anxiety group will complete assessments at four timepoints: baseline and 2, 6, and 12 months. The healthy control group will be assessed at baseline and 12 months. The timepoints were chosen to efficiently assess symptom improvement at 2 months, check for relapse at 12 months for the clinical anxiety group, and confirm continued health for the healthy control group. These intervals also minimize participant burden while ensuring comprehensive data collection over the course of a year. Assessments will include clinical interviews, standardized self-report questionnaires, computerized neurocognitive testing, VR-based behavioral evaluations, physiological recordings (EEG and ECG), and multimodal brain imaging (structural, functional, and diffusion MRI).

Given the 12-month follow-up period and the multimodal nature of the assessments, challenges related to participant burden and attrition are anticipated. To mitigate these risks, the study incorporates flexible scheduling, abbreviated interim assessments at selected follow-up visits, and the option for remote administration of questionnaires where appropriate. These strategies are intended to support participant retention and ensure data completeness while maintaining methodological rigor.

Figure 2 summarizes the timing and scope of these assessments across both groups. At each timepoint, specific instruments have been selected to capture transdiagnostic symptom dimensions and neurobehavioral mechanisms aligned with the RDoC framework—particularly domains related to Negative Valence Systems, Cognitive Systems, and Arousal/Regulatory Systems.

#### 2.5.1. Clinical Assessments

Clinical assessments will be conducted at the baseline and 12-month follow-up for all participants. Each session will be administered by a board-certified psychiatrist or trained research personnel. The assessment will include the collection of sociodemographic variables such as age, sex, education level, marital status, occupation, alcohol use, smoking status, height, and weight. Additionally, a structured evaluation of psychiatric history will be performed, including the onset and duration of anxiety symptoms, previous psychiatric diagnoses and treatments (treatment type, dosage, duration), and family history of psychiatric disorders.

These data will provide essential contextual information for interpreting behavioral, physiological, and neuroimaging findings, and for exploring clinical predictors of treatment response and prognosis. Some of these data will also be used as independent variables in the analysis.

#### 2.5.2. Evaluation of Anxiety Symptoms and Associated Psychiatric Conditions

To comprehensively assess anxiety and related cognitive-affective constructs, multiple validated self-report measures will be administered. Each instrument serves a distinct role within the analytic framework. Key clinician-rated and self-report instruments include the Panic Disorder Severity Scale (PDSS), the Depression Anxiety Stress Scales-21 (DASS-21), the Generalized Anxiety Disorder-7 (GAD-7), the Intolerance of Uncertainty Scale (IUS), and the Anxiety Sensitivity Index-Revised (ASI-R). Each instrument serves a distinct analytic role within the study framework. The PDSS functions as the primary measure of panic-related symptom severity and behavioral avoidance and is used to define treatment response. The DASS-21 Anxiety subscale serves as a secondary outcome reflecting generalized physiological and cognitive anxiety, while the GAD-7 provides a complementary index of generalized worry and assists in screening for comorbid anxiety presentations. The IUS and ASI-R act as mechanistic predictors, capturing cognitive and interoceptive vulnerability dimensions that contribute to anxiety maintenance.

Neurocognitive functioning will be evaluated using the CNS Vital Signs battery, while stress exposure will be assessed using the Stress and Adversity Inventory. Affective states will be measured using the Positive and Negative Affect Schedule (PANAS), which assesses momentary affective experiences across two dimensions: positive and negative affect. The Behavioral Inhibition and Activation Systems (BIS/BAS) scales will be included to evaluate motivational and affect-regulatory tendencies. These measures contribute to the RDoC Arousal and Regulatory Systems domain, capturing interindividual variability in emotional and motivational responsiveness.

To reduce participant burden and ensure longitudinal feasibility, shortened versions of selected questionnaires will be administered at interim visits (2 and 12 months). Remote administration via telephone or a secure institutional online platform may be employed as appropriate. All remote procedures will use validated formats and standardized instructions to maintain reliability and data comparability across timepoints. Detailed descriptions of each instrument—including theoretical constructs, administration procedures, psychometric properties, and language validation—are provided in the Supplementary Material (Table S1).

#### 2.5.3. VR-Based Behavioral Assessment

A VR environment will be used to assess anxiety-related behavioral responses in an ecologically valid and controlled setting. The system integrates physiological, behavioral, and neural data streams during exposure to anxiety-inducing scenarios.

The VR assessment will span approximately 30 min, including a 20-min task conducted within a fully immersive environment. The platform is built on the previously validated Virtual Reality Assessment for Panic Disorder (VRA-PD), which originally comprised three modules: daily environment exposure (M1), relaxation (M2), and interoceptive exposure (M3) [25]. In the validation study by Kim et al., the VRA-PD successfully distinguished patients with panic disorder from healthy controls across multiple physiological and subjective indices [25]. In this protocol, the interoceptive exposure module (M3) was excluded to reduce participant burden and improve data quality. In the original VRA-PD feasibility study [25], M3-related data were partially excluded due to user discomfort and motion-related physiological artifacts. Consistent with these findings, recent VR-based predictive modeling studies also excluded M3 to minimize movement- and respiration-related noise. Accordingly, the structure and content of M1 and M2 have been retained.

Although initially designed for panic disorder, the paradigm targets fundamental threat-related processes—anticipatory anxiety, avoidance, and physiological arousal—that are shared across anxiety disorders. The M1 (daily environment exposure) module induces claustrophobic and social-evaluative anxiety by requiring participants to enter and remain in an elevator occupied by several virtual avatars, while the M2 (relaxation) module trains diaphragmatic breathing and progressive muscle relaxation to assess recovery dynamics. This structure enables examination of both anxiety induction and regulation within ecologically valid environments. Stimuli are presented through an immersive head-mounted display (Oculus Quest Pro; Meta Platforms, Menlo Park, CA) with a native resolution of 1800 × 1920 pixels per eye, 90 Hz refresh rate, and a 106° field of view. Built-in off-ear speakers deliver synchronized auditory cues to enhance realism and immersion. The system supports 6-degree-of-freedom (6DoF) tracking and built-in eye and facial-expression tracking, which enable the recording of gaze fixation and subtle behavioral responses. Each module lasts approximately 10 min, and the total VR session duration is about 25 min.

All stimuli are implemented in Unity 3D 2022, with standardized lighting, ambient sound, avatar animation, and environmental layout to ensure reproducibility across participants and sessions. Task scripts automatically control scenario timing, transitions, and data logging, allowing identical exposure parameters for all participants.

Behavioral metrics such as task completion time, in-environment decisions, and subjective responses will be collected throughout the task. These data, alongside physiological signals, allow for high-resolution multimodal characterization of individual anxiety responses.

This refined VR system enables repeated and scalable deployment in both clinical and research settings. It is conceptually aligned with the Potential Threat construct in the Negative Valence Systems domain of the RDoC framework.

Task delivery scripts, environmental parameters, and timing are fully automated to ensure identical exposure across participants and sessions. All raw and event-timed data are timestamp-synchronized and stored for reproducibility. Prior testing confirmed high within-session reliability of anxiety ratings and heart rate variability (HRV) measures [25]. Through this adaptation, the VR paradigm provides a standardized yet ecologically rich framework for probing shared mechanisms of anxiety beyond diagnostic boundaries.

#### 2.5.4. EEG and ECG Acquisition

Continuous electrophysiological activity will be acquired using a 20-channel wireless EEG system (Enobio; Neuroelectrics, Barcelona, Spain), which allows simultaneous EEG and ECG acquisition within the VR environment. Nineteen scalp electrodes will be positioned according to the international 10–20 system, and one additional channel will record a single-lead ECG from the chest. All sensors use Ag/AgCl electrodes with an impedance kept below 10 kΩ. Data will be sampled at 500 Hz (24-bit resolution) with a 0.1–100 Hz online band-pass filter and referenced to the common-average reference.

EEG/ECG streams are hardware-synchronized with VR event triggers and behavioral data through a shared digital timestamp system, allowing precise temporal alignment across modalities. This configuration supports combined analyses linking neural oscillatory dynamics and autonomic responses to VR-elicited anxiety behavior.

#### 2.5.5. Behavioral and Postural Tracking

Upper-body posture and movement during the VR tasks will be continuously captured using the AVATAR Studio system [29]. The original AVATAR platform reconstructs 3D body motion in real time using a multi-camera, markerless tracking architecture and deep-learning-based body-part detection (AVATARnet), enabling high-resolution behavioral quantification in mice.

In the present study, the system will be configured for human participants using four infrared cameras positioned to ensure full-angle visibility and minimal occlusion. The resulting three-dimensional skeletal joint trajectories (60 Hz) will be treated as four-dimensional spatiotemporal data (x, y, z × time) and analyzed using unsupervised learning approaches to derive latent movement representations. These data-driven behavioral representations will be used to characterize patterns such as postural freezing, avoidance behavior, and upper-body displacement during VR tasks. Derived motion features will be synchronized with EEG, ECG, and VR event data for multimodal integration. Depending on the analytic aims, both kinematic and temporal–dynamical models (e.g., movement entropy, transition-state clustering) may be applied to characterize behavioral responses.

#### 2.5.6. Brain MRI Acquisition

Brain MRI will be acquired using clinical-grade MRI equipment (A 3 T Philips Ingenia scanner, Philips Healthcare, Best, The Netherlands) at the Yonsei Convergence Medical Technology Center (Seoul, Republic of Korea). The proposed MRI machine is a 3.0-T Philips Ingenia CX (Philips Healthcare, Best, The Netherlands). The scan will take approximately 40 min, capturing T1 3D coronal structural brain images, resting-state functional brain images (fMRI), and diffusion-weighted images (DWI). MRI acquisition will follow a standardized protocol designed to assess cortical structure, intrinsic functional connectivity, and white matter integrity.

Structural imaging will be acquired using a 3D T1-weighted magnetization-prepared rapid gradient echo sequence to assess cortical thickness and gray matter volume. Resting-state fMRI will be collected with participants instructed to remain still with eyes closed and to avoid focused thinking, enabling assessment of intrinsic functional connectivity. DWI will be used to evaluate white matter integrity through metrics such as fractional anisotropy and mean diffusivity.

Participants will wear earplugs and headphones for acoustic protection and will be stabilized using foam pads to minimize motion artifacts. MRI contraindications (e.g., metallic implants, pregnancy) will be screened prior to scanning. A trained research assistant will be present throughout to monitor for distress or discomfort.

### 2.6. Outcomes and Operational Definitions

The primary outcome of this study is treatment response, operationally defined as a clinically meaningful reduction in panic symptom severity. Responders are defined as participants who achieve a ≥40% decrease in the total score of the PDSS from baseline to each follow-up assessment (2, 6, and 12 months), while participants not meeting this criterion are classified as non-responders.

This threshold was selected based on prior evidence indicating that a 35–45% decrease on disorder-specific anxiety scales corresponds to clinically meaningful improvement and early treatment benefit [30,31]. The 40% criterion also provides adequate sensitivity for detecting within-subject improvement across multiple timepoints in longitudinal designs.

To ensure conceptual coherence with the study’s transdiagnostic framework, additional analyses will examine changes in the GAD-7, DASS-21 Anxiety subscale, and LSAS as secondary outcomes, and the consistency of responder classification across these measures will be evaluated. This multi-metric approach retains sensitivity to panic-specific reactivity while enabling comparability with broader anxiety-disorder literature.

These operational definitions allow for both categorical classification (responder vs. non-responder) and continuous modeling of symptom change, facilitating the integration of clinical, behavioral, physiological, and neuroimaging predictors across the 12-month follow-up.

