## Abstract

**Background/Objectives**: Anxiety disorders are highly prevalent and impairing psychiatric conditions. Conventional diagnostic approaches based on symptom checklists lack biological specificity and often fail to guide treatment decisions effectively. This study protocol outlines a multidimensional, prospective investigation designed to identify behavioral and neurobiological biomarkers predictive of treatment response in individuals with anxiety-related symptoms, grounded in the Research Domain Criteria framework. **Methods**: This observational, longitudinal study (NCT06773585) will include a transdiagnostic sample of clinical anxiety group alongside a healthy control group (185 participants, including 145 patients with anxiety disorders and 40 healthy controls). Participants will undergo comprehensive baseline assessments, including clinical interviews, self-report questionnaires, a virtual reality (VR)-based behavioral task, electroencephalography (EEG), electrocardiography (ECG), and structural and functional brain magnetic resonance imaging. Follow-up assessments will be conducted at 2, 6, and 12 months, with recruitment and data collection planned from 2024 to 2029. These complementary modalities are integrated to capture behavioral, physiological, and neural indicators of anxiety and its treatment response. Multimodal baseline features will be used to construct machine-learning models predicting treatment response, defined as ≥40% reduction in anxiety severity scores. Longitudinal analyses will examine symptom trajectories and neural mechanisms associated with response. Neurobiological comparisons will be made across timepoints and between responders, non-responders, and healthy controls. **Conclusions**: By identifying objective, biologically grounded markers of anxiety and treatment response, our findings will contribute to the development of personalized assessment tools and scalable digital interventions for psychiatric care.

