#### 2.2.1. Inclusion Criteria

The inclusion criteria for the clinical anxiety group are (1) adults aged between 19 and 60 years; (2) currently diagnosed with an anxiety disorder based on DSM-5 criteria, specifically including panic disorder, SAD, GAD, agoraphobia, or specific phobia, confirmed by a board-certified psychiatrist (individuals who have been previously treated for anxiety are not included); (3) ability to understand the purpose and procedures of the study and provide written informed consent, and (4) no history of major neurological disorders or psychotic illness.

The inclusion criteria for the healthy control group are (1) adults aged between 19 and 60 years; (2) no current or past psychiatric diagnoses and not currently using any psychotropic medication; and (3) ability to fully understand the purpose and procedures of the study and provide written informed consent.

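### Primary response is a 40% fall on a panic scale for all five eligible diagnoses with no baseline floor, so a low baseline score can fix the label whatever the treatment did

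*Protocol article*

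**What the plan says.** Section 2.2.1 admits patients with any of five DSM-5 diagnoses, "specifically including panic disorder, SAD, GAD, agoraphobia, or specific phobia". Neither 2.2.1 nor 2.2.2 requires panic disorder or a minimum PDSS score.

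Section 2.5.2 gives the PDSS its role: "The PDSS functions as the primary measure of panic-related symptom severity and behavioral avoidance and is used to define treatment response".

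Section 2.6 sets the outcome for the whole clinical group: "The primary outcome of this study is treatment response, operationally defined as a clinically meaningful reduction in panic symptom severity". The rule built on it applies at 2, 6 and 12 months: "Responders are defined as participants who achieve a ≥40% decrease in the total score of the PDSS from baseline to each follow-up assessment". Anyone who misses the threshold falls into a default class, in the words "while participants not meeting this criterion are classified as non-responders". The section supports the 40% cut-off with evidence from scales specific to the disorder under study. It makes GAD-7, DASS-21 Anxiety and LSAS secondary outcomes, plans to check how consistently the measures classify responders, and allows continuous modelling of change.

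Section 3.3 uses the PDSS label as the target of the primary machine-learning models, and the captions of Figures 1 and 3 repeat it. The Abstract is looser: "predicting treatment response, defined as ≥40% reduction in anxiety severity scores". Sections 1 and 2.6 describe the aim or framework as transdiagnostic.

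**The concern.** A panic scale measures response well in patients who have panic symptoms to lose. For a patient treated for social anxiety, worry or a specific phobia, it may start at or close to zero. A percentage-change rule then behaves badly in two ways: at zero the threshold cannot be reached, and just above zero a trivial change crosses it. In neither case does the label describe what happened to the disorder being treated.

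This label is the outcome of the primary analysis. The candidate features in 3.3 include psychiatric history and psychometric scores, which carry information on diagnosis. A model could look predictive by recognising who has panic disorder. Cross-validation would not expose this, because training and test folds share the same label. The responder versus non-responder imaging comparisons in 3.2 adjust for age and sex, and the potential covariates listed in 3.4 do not name diagnosis. A diagnostic difference could therefore be reported as a neural marker of response.

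**Working it through.** **Is there a planning figure to reproduce?** Not for the outcome definition. The only planning figure that uses the label is in 2.7 (145 patients, 20% dropout, 25% non-response, 80 non-responders). It gives 145 × 0.80 × 0.25 = 29, not 80. That is a separate matter, and nothing below depends on it.

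**Step 1: points needed to be a responder.** With whole-number scores and baseline b, the smallest qualifying fall is the smallest whole number d with d/b ≥ 0.40.

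| Baseline PDSS | Smallest qualifying fall | Percentage |
|---|---|---|
| 0 | none possible | 0/0, undefined |
| 1 | 1 | 100% |
| 2 | 1 | 50% |
| 3 | 2 (1 point is 33%) | 67% |
| 5 | 2 | 40% |
| 8 | 4 | 50% |
| 12 | 5 | 42% |

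At baseline 0, the default clause in 2.6 turns an undefined percentage into a non-response.

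**Step 2: labels when nothing changes.** This is an illustration on assumed inputs. True score is held constant; baseline and follow-up each add normal error with SD 1, 1.5 or 2 points, rounded and kept within an assumed range of 0–28, with 400,000 draws per setting. Among draws with observed baseline above 0, the share labelled responder at one visit is:

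| True score | SD 1 | SD 1.5 | SD 2 |
|---|---|---|---|
| 1 | 48% | 54% | 57% |
| 2 | 28% | 38% | 45% |
| 3 | 16% | 27% | 35% |
| 12 | 0% | 0.4% | 2% |

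The documents give neither the error SDs nor the scale range. Step 1 depends on neither.

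**Step 3: does the threshold's rationale carry over?** Section 2.6 rests the 40% on disorder-specific scales, and 2.5.2 describes the PDSS as panic-related. For social anxiety disorder, GAD and specific phobia, it is not such a scale, so the stated rationale does not reach those patients.

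**Step 4: can the number of affected labels be found?** It would need the share of patients without panic disorder and the share of those scoring about 0–2 on the PDSS. Neither is given. Assuming 20–60% for the first and 25–75% scoring exactly 0 for the second, the non-responders by construction among 116 completers (145 × 0.80) run from 116 × 0.20 × 0.25 = 5.8 to 116 × 0.60 × 0.75 = 52.2. A range of about 6 to 52 reflects the assumptions and is no estimate.

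**The case against.** The strongest reply is that low PDSS scores in patients without panic disorder are inferred, not documented. Section 2.5.2 says that the scale also covers behavioural avoidance, which need not be absent in agoraphobia, social anxiety or phobia. Comorbid panic is not excluded by 2.2.2, and 2.3 screens for comorbid conditions. This stands: the documents show that the rule permits such labels, not how often they will occur.

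Second, 2.6 itself recognises the tension. The secondary scales, the consistency check and continuous modelling let the transdiagnostic question be examined, and 3.4 calls all analyses exploratory. This also stands, but none of it alters the primary label or the target of the models in 3.3.

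Third, handling of a zero baseline might be left to an analysis plan that is not shown. This stands only in part. The article does not stay silent: it states the default that makes these patients non-responders, and it chooses the PDSS for everyone.

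A reader might go further and infer that every label outside panic disorder is invalid, for example 20–60% of 145, or 29 to 87, against about 29 expected non-responders. The documents do not support that. The share is assumed; only very low baselines are affected, not every non-panic patient; 145 counts enrolled patients while 29 counts completers; and baselines of 1–2 produce false responders as well, so errors run both ways.

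**Conclusion.** The concern holds as a defect in a stated rule. Primary response is panic-specific in a group that need not have panic disorder, and no baseline floor protects the percentage. The consequences at baseline 0 (never a responder) and at 1–2 (one point decides) are exact, given whole-number scores. That the label may partly encode diagnosis follows if patients without panic disorder tend to score low. This is a reasonable inference from the scale's stated role, but the documents do not show it. The number of affected labels and the net direction of error are unknown.

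A reader might also infer that the transdiagnostic objective cannot be answered at all. That is too strong, because the secondary and continuous analyses address it in part. Nor does the Abstract's general wording establish a conflicting definition; it reads as a loose summary that should be aligned. The point still needs repair before analysis, because the label is the target of the primary models.

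**What to change.** In 2.6 and 3.3, adopt one of two definitions:

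- **(a)** Limit the PDSS response label, and the models trained on it, to participants at or above a pre-set baseline PDSS floor, and define the transdiagnostic response label on another scale already collected.
- **(b)** Define primary response on the scale matched to the principal diagnosis, for example PDSS for panic disorder or agoraphobia, LSAS for social anxiety disorder and GAD-7 for GAD. The rule for principal diagnosis must be written down. A scale for specific phobia must also be chosen, since none of the instruments named in the article is described as specific to it.

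Under either option:

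- set a minimum baseline score for every scale used, so that zero and near-zero baselines are not labelled by default;
- include diagnosis as a covariate, or report a diagnosis-only benchmark model that the multimodal models must beat;
- report performance by principal diagnosis;
- confirm that each scale is collected at baseline and at 2, 6 and 12 months, given the shortened questionnaires planned for some visits;
- align the Abstract and figure captions.

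The cost is mainly wording, with instruments already named. Option (a) uses fewer patients for the PDSS models. Option (b) pools different scales, so the label is less uniform, and it can still carry diagnosis information, which is why the benchmark is needed there too.
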